### VII. RISKS AND DISCOMFORTS

Patients will be informed that there are no foreseeable physical risks from this research study. They will be informed that they may feel uncomfortable completing various psychological questionnaires and that they may find it time-consuming to participate in weekly 90 minute groups.

As Zoom is HIPPA approved and secure, there are no risks associated with its use. However, patients will be asked to ensure that they are in a private room during the group sessions, to protect their privacy and that of group members.

As with any group studies, there may be confidentiality issues, but we will discuss the importance of maintaining confidentiality at the beginning of each group.

### VIII. POTENTIAL BENEFITS

Patients will be informed that there may be no direct benefit from participating in this research study. Some patients may become better able to cope with stress and NF symptoms, and experience improved quality of life.

In the future, knowledge from this research study may benefit others by providing information on how such interventions can help patients with neurofibromatosis 1, neurofibromatosis 2, and schwannomatosis

### IX. MONITORING AND QUALITY ASSURANCE

Electronic information will be stored in REDCap (Research Electronic Data Capture), a free, secure, and HIPAA-compliant web-based application hosted by the Partners HealthCare Research Computing Enterprise Research Infrastructure & Services (ERIS) group (based at the PHS Needham corporate datacenter). Data will be stored on password protected computers that will be stored in secure locations at all times. Paper data files (with coded subject identification) will be stored in a locked filing cabinet. Only research staff will have access to these data locations.

A unique anonymous identifier will be assigned to each subject; subsequently, all data collected will be associated exclusively with this identifier. This includes all questionnaires administered over the course of the study, as well as home practice logs. Data from this study will be stored for three years after the publication of all study results, at which time all paper data files will be shredded and computer files will be deleted.

#### Data Management and Quality Control Procedures

To maximize accuracy and security, all survey data will be collected and stored on REDCap. Research staff will ensure that proper consent has been obtained before sending the REDCap survey to each participant.

REDCap (Research Electronic Data Capture) is a free, secure, HIPAA compliant web-based application hosted by the Partners HealthCare Research Computing Enterprise Research Infrastructure & Services (ERIS) group. Vanderbilt University, with collaboration from a consortium of academic and non-profit institutional partners, has developed this software toolset and workflow methodology for electronic collection and management of research and clinical study data. Data collection projects rely on a study-specific data dictionary defined by members of the research team with planning assistance from Harvard Catalyst, The Harvard Clinical and Translational Science Center EDC Support Staff. This iterative development and testing process results in a well-planned data collection strategy for individual studies. Using REDCap, the research team can also design web-based surveys and engage potential respondents using a variety of notification methods. REDCap provides flexible features that can be used for a variety of research projects and provides an intuitive interface to enter data with real time validation (automated data type and range checks). The system offers easy data manipulation with audit trails, reports for monitoring and querying participant records, and an automated export mechanism to common statistical packages (SPSS, SAS, Stata, R/S-Plus).

Since consistency of application of the study protocol is critical to acquiring high quality data, all research personnel have undergone or will undergo a competency-based training program prior to enrolling subjects.

### **Data and Safety Monitoring Plan**

Adverse Event Monitoring: Throughout the study subjects will be monitored for the occurrence of events defined as any undesirable experience or unanticipated risk. Lack of effect of treatment is not considered an event. All adverse events will be reported on an adverse event form. The Principle Investigator has the responsibility of reporting serious adverse events (death, life threatening illness or injury, serious injury, or permanent disability) to PHRC within 24-72 hours of notification.

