## MIND-BODY SKILLS TRAINING FOR ADULTS WITH NEUROFIBROMATOSIS

Neurofibromatosis clinic at MGH (900 visits/year in 2014) and 2) the Children's Tumor Foundation (CTF). Our IRB approved flyers will be posted in various areas of the hospital and emailed periodically to patients in the NF registry via CTF, which includes local (within the United States) and international (outside of the United States) patients. We have used this method of recruitment successfully in our preliminary clinical trial ([name] PI, funding from CTF). CTF has committed their support to recruitment, should this study be funded, and DoD has allowed for recruitment of patients within and outside of the United States. This method of recruitment is advantageous because it has allowed us to recruit patients from across the U.S. and Canada, thus fostering generalizability of results. We do not anticipate any difficulties recruiting, based on our success with working with this population. However, if difficulties occur, we plan to expand our recruitment to other U.S. NF centers with whom we have collaborations, including Children's Hospital in Boston and Johns Hopkins NF Clinic. We will also be recruiting by posting our study on Partners Clinical Trials.

Recruitment will also occur through the Research Patient Database Registry (RPDR). The RPDR is a centralized clinical data registry that gathers data from various hospital legacy systems and stores it in one place. Researchers access the data using the RPDR online Query Tool. They may query the RPDR data for aggregate totals, and with proper IRB approval, obtain medical record data. The RPDR ensures the security of patient information by controlling and auditing the distribution of patient data within the guidelines of the IRB and with the use of several built-in, automated security measures. To identify potentially eligible patients:

- 1) A RPDR query will be performed to identify those patients with chronic pain diagnoses. Study staff will review the medical record to confirm potential participant eligibility and to identify their linkage to an MGH primary care physician. Access to patients' medical records will be restricted to this pre-enrollment recruitment phase.
- 2) Study staff then will obtain permission for initial contact from each potentially eligible patient's PCP by having providers review letters and discard ones that they do not approve.

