### **Administered Pre-Intervention, Post-Intervention, 6 and 12 Month Follow-Ups:**

Quality of Life (WHOQOL-BREF) physical health scale – co- primary outcome.

Quality of Life (WHOQOL-BREF) psychological scale – co- primary outcome.

Quality of Life (WHOQOL-BREF) social relationships scale – secondary outcome.

Quality of Life (WHOQOL-BREF) environmental scale – secondary outcome.

The Patient-Health Questionnaire Depression (PHQ-9) – secondary outcome/mediator

The Generalized Anxiety Disorder Questionnaire (GAD-7) – secondary outcome/mediator

MOS Social Support Survey – secondary outcome/mediator

The Gratitude Questionnaire Six Item Form (GQ-6) – secondary outcome/mediator

Revised Life Orientation Test (LOT-R) – secondary outcome/mediator

Measure of Current Status Part A (MOCS-A) – secondary outcome/mediator

Cognitive and Affective Mindfulness (CAM) – secondary outcome/mediator

Perceived Stress Scale 10 (PSS-10) – secondary outcome/mediator

Interpersonal Reactivity Index (IRI) Empathic Subscale – secondary outcome/mediator

PROMIS Pain Interference v8 – secondary outcome/mediator

Graded Chronic Pain Scale (GCPS) – secondary outcome/mediator

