# MIND-BODY SKILLS TRAINING FOR ADULTS WITH NEUROFIBROMATOSIS

Patient Homework –weekly during intervention:

Progress Note – adherence to treatment/skill consolidations/moderator.

Administered Post-Intervention, 6 and 12 Month Follow-Ups Only:

Patient Perception of Improvement – anchor-based measure of improvement

Figure 1. Study Design.

[figure not shown]

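### Adverse events are to be monitored throughout the study, but the listed schedule has no general adverse-event enquiry common to both arms, and the serious-event list omits hospital admission

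*Protocol*

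**What the plan says.** The Data and Safety Monitoring Plan (protocol section IX) sets a wide definition and a continuous period: "Throughout the study subjects will be monitored for the occurrence of events defined as any undesirable experience or unanticipated risk". It adds one exclusion, "Lack of effect of treatment is not considered an event", and a recording rule, "All adverse events will be reported on an adverse event form". Expedited reporting applies to "serious adverse events (death, life threatening illness or injury, serious injury, or permanent disability) to PHRC within 24-72 hours of notification". The plan does not say who asks about events, when, or with what question.

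Section V presents its list of assessments as itemised. It has a baseline demographic form, a set headed "Administered Pre-Intervention, Post-Intervention, 6 and 12 Month Follow-Ups", weekly homework and progress notes during the intervention, and at the three follow-ups a "Patient Perception of Improvement – anchor-based measure of improvement".

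Three other places bear on safety:

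- Section IV (Subject Enrollment): REDCap texts the principal investigator if PHQ-9 item 9 is endorsed at any of the four time points, and a safety procedure starts. The principal investigator is also informed of every self-harm incident, however it is found.
- Section VI (analyses for the primary aim): the global rating has two worse categories. It is used to judge what change in quality of life matters to patients.
- Section I (description of the 3RP): each 3RP session opens with a short check of recent stress and medical symptoms.

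**The concern.** A promise to monitor everything undesirable throughout the study needs a means of finding out. Where participants are not asked, the number of events recorded depends on who volunteers information and who happens to be in contact with staff. That gives two problems. A low count says little about whether either program is safe. A difference between arms, or the lack of one, may reflect different opportunities to report.

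The serious-event list raises a separate question. It is closed, with four terms, and hospital admission is not one of them. In an NF population, admissions for medical or psychiatric reasons are foreseeable: the comorbidity exclusion covers only conditions not related to NF, so participants whose NF may worsen are eligible.

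**Working it through.** The safety section states no figure, so there is none to reproduce. The check sets the passages side by side.

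**1. Does any listed assessment ask about events in general?**

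| Listed item (section V) | When | General event enquiry? |
|---|---|---|
| Demographics | Baseline | No |
| 15 self-report scales (WHOQOL-BREF counted as 4 domains, plus 11 others) | Baseline, post-test, 6 and 12 months | No; PHQ-9 item 9 asks about suicidality |
| Homework and progress note | Weekly during sessions | No; described as adherence and skill consolidation |
| Patient Perception of Improvement | Post-test, 6 and 12 months | No; rates overall change, including worse |

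So no listed item asks about new medical problems, emergency visits or admissions. The depression, anxiety, stress and pain scales record symptom levels at a visit. They do not record what happened between visits.

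**2. Are the safety signals that are collected tied to the event record?** Item 9 leads to an alert and a safety procedure (section IV). The worse ratings feed the assessment of important change (section VI). Neither passage mentions the adverse event form, and the monitoring plan mentions neither signal.

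**3. How long does capture rest on spontaneous report?** There are 8 weekly sessions, then assessments at 6 and 12 months. Taking 12 months as 52 weeks from the start of the sessions, 52 − 8 = 44 weeks have no session contact. If the 12 months run from post-test, the period is longer. In that time the only scheduled contacts described are the two online batteries. This is the length of the unprompted period. It does not measure how many events are missed.

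**4. Is detection the same in both arms?** The session-by-session symptom check is described for the 3RP. Section V.1.2 says the HEP-NF sessions share the format and receive equal therapist attention, but does not mention this check. Equal detection during the sessions is therefore possible but not stated.

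**5. What happens to a hospital admission?** Take a psychiatric admission with no injury, or a short NF-related admission that is not life threatening. Either is an undesirable experience, so it belongs on the adverse event form once known. If it involves no death, life-threatening condition, serious injury or permanent disability, it meets none of the four terms and no expedited report follows.

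**The case against.** The strongest reply is that this is a low-risk behavioural trial which already screens for the gravest harm it anticipates. Suicidality is asked about at four time points with an automatic alert, self harm reaches the principal investigator by any route, and every event that comes to light is recorded. Safety is not among the specific aims. All of this is correct. It confines the point to other events and to linkage, and keeps it away from the efficacy conclusions. It does not supply the missing enquiry.

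A reader might go further in several ways that the protocol does not support:

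- *Nothing scheduled asks about harm.* Item 9 and the global rating do, within their scope.
- *Worsening is excluded by rule as lack of effect.* The exclusion covers lack of effect only, and the definition of an event is wide enough to include deterioration on a plain reading. No sentence lets staff set deterioration aside.
- *The harms that the protocol names would go unrecorded.* Self harm is escalated and survey answers are stored in REDCap. The other named risks are questionnaire discomfort, time burden and group confidentiality.
- *The pilot data show how much harm would be missed.* With the HEP-NF mean change in Physical Health QoL of 0.12 (61.06 − 60.94), the change SD of 14.7 and a normal approximation, Φ((−6.25 − 0.12)/14.7) = 33% fall by more than 6.25 units. By the same formula, Φ((0.12 − 6.25)/14.7) = 34% rise by more than 6.25. That is nearly symmetric spread around no change and does not count missed events.
- *The reporting time sets two deadlines.* It reads as a range with a 72-hour outer limit.
- *Record access after enrolment is barred for everyone.* That limit sits within one recruitment route and does not carry this point.

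**Conclusion.** The point holds in a limited form. The protocol promises monitoring throughout the study, but its itemised schedule contains no general adverse-event enquiry that is the same in both arms. The two safety signals it does collect are not linked to the adverse event form. After the sessions end, other events are known only if participants volunteer them, and detection could differ by arm. Separately, an admission that fits none of the four serious terms would be recorded if known but not reported on the expedited timetable.

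Its size is modest. The primary and secondary efficacy analyses do not change. What is weakened is any later statement about safety that rests on the event count. How events are elicited and which are serious belongs in the protocol, so a statistical analysis plan that is not shown would not be expected to close the gap.

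The conclusion assumes that the list in section V is complete, as its description as itemised suggests. The questionnaire attachment and the adverse event form are not shown. If either carries a general event question at the follow-ups, the first part falls away. The omission from the serious-event list would remain.

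**What to change.** 1. Add one short REDCap adverse-event form, identical in both arms, at post-test, 6 months and 12 months. It should ask about new or worse medical or psychological problems, emergency visits and hospital admissions since the last assessment. State in the monitoring plan that a positive answer, a positive PHQ-9 item 9 or a substantially worse rating prompts review for the adverse event form.
2. Add inpatient admission, medical or psychiatric, to the serious-event list in the Data and Safety Monitoring Plan.

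The cost is a minor amendment, a few minutes per participant at three time points that already exist, and more event forms to process. No new visits are needed. If the attachment already contains such a question, citing it in section IX and stating the link to the adverse event form would replace the new form.
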